### Data collection timepoints

In order to minimise cost and participant burden for this trial, and since the main purpose of the trial is to test study processes and procedures, data will only be collected at a maximum of three occasions per site: at the end of the control period, and at 3 and 6 months after the end of the intervention in each site. Sites 1 and 6 will not have a control period, and sites 5 and 10 will not have a post-intervention period, in order to minimise the duration of the study for which there is no concurrent vertical comparison between control and post-intervention periods. To increase the response rate, participants will be paid a small amount (£5 end of control period and £10 for 3 months data) for taking part in data collection.

### Assessment of unanticipated outcomes

We will provide each contact centre with a sheet to record harms such as injuries as a result of using the equipment. The contact centre staff will be made aware of this and be asked to record any harms they think are a result of the intervention. We will ask them to detail the type of activity where the harm occurred, the type of harm (e.g. injury) and the date and time. We will collate this data from all contact centre every three months. We will also use the focus groups as a way of eliciting any unintended consequences.  Adverse events will also be a standing item on all Study Management and Study Steering Committee meetings.

Control/comparator group

Waiting list control – all 10 sites will receive no intervention for between 3 and 12 months after study set-up is complete; then they will receive the intervention.

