**Contact centres and health**

Due to their occupational nature, contact centres are currently one of the most sedentary working environments, with some members of staff reporting up to 95% of their shift spent sitting. The technology in contact centres prevents staff from regularly leaving their desk and many call handlers often report stressful work environments due to low workplace autonomy, strict supervision of individual performance and commission-based salary systems [33]. One in four members of contact centre staff regularly experience musculoskeletal problems with 22.4% of sick days lost to such problems [30].  A recent study found that a common factor for sedentary behaviour shared by contact centre agents, team leaders and senior staff included a considerable lack of knowledge and awareness of sedentary behaviour as a risk factor for poor health in highly sedentary workplaces [27]. Additionally, there was also a low level knowledge among staff of guidelines and recommendations relating to sedentary behaviour and physical activity in the workplace and often there is no reflection of this in organisational policies [27, 34].

In 2012, a study found that working in a contact centre was associated with higher levels of sedentary behaviour than other office-based work [4]. Another study [35], hypothesised that the culture and policies of a contact centre may differ from other office-based work and thus present a unique setting.

As well as being a highly sedentary workplace, work in contact centres has been described as ‘constrained’ work, where opportunities for enrichment and intrinsic reward are apparently limited [26]. Contact centre agents have voiced concerns over job security, performance monitoring and a desire for increased autonomy over their working practices as influential factors for their motivation to participate in strategies to reduce sedentary in the workplace [27]. However, organisational pressures to maintain high levels of productivity and meet targets frequently work against organisational investment into health and physical activity programmes within some contact centres. This is often due to perceptions that these activities will reduce the agents’ call making time and lead to productivity losses [36]. One study reported that leaders and senior staff had ‘identified a conflict between promoting productivity and targets to call agents, while encouraging them to move more and sit less’ [27].

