## Randomisation

Randomisation will occur in month three. The unit of randomisation is contact centres. A computer-generated block randomisation algorithm will be used to randomly allocate each contact centre to start the intervention at one of five time points, three months apart. Randomisation in this way allows us to introduce the intervention to each site in an unbiased way unrelated to time or the particular circumstances of each site. It also helps ensure there is approximate balance on average across all the intervention start times in terms of participant or contact centre characteristics.

Steps to minimise bias

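### The harms sheet records only what staff blame on the intervention, so workplace injuries have no waiting-period comparator

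*Protocol*

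**What the plan says.** All of the harms procedure stands in the protocol under Assessment of unanticipated outcomes. The tool is a sheet: "We will provide each contact centre with a sheet to record harms such as injuries as a result of using the equipment". Staff are told of it and will "be asked to record any harms they think are a result of the intervention". They are to "detail the type of activity where the harm occurred", together with the kind of harm and its date and time. Collection covers every centre: "We will collate this data from all contact centre every three months".

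Two further routes follow in the same section. One is qualitative: "We will also use the focus groups as a way of eliciting any unintended consequences". The other is committee oversight, with adverse events on the agenda of every management and steering meeting. No separate way of collecting those events is described.

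On waiting time, the Control/comparator group paragraph says that "all 10 sites will receive no intervention for between 3 and 12 months after study set-up is complete". The Randomisation section has each centre "start the intervention at one of five time points, three months apart".

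**The concern.** A harms log is most useful when it records what happened and leaves the cause to be judged afterwards. Here the causal judgement comes first and is made by the person filling in the sheet. An event screened out at that stage cannot be recovered by later review, because it was never written down.

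The trial has randomised waiting time in which ordinary workplace injuries could be counted on the same form and set beside the count after the start. The entry rule gives that up, although the sheet is already given to each centre and collated from all of them.

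This matters here for two reasons. The case for the design, in Design and methods, rests partly on the belief that the intervention is unlikely to do harm, and a log that filters on staff belief is a weak test of it. Aim 2 also asks whether the study procedures are fit for a confirmatory trial, so a form with this filter could be carried forward.

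**Working it through.** The protocol states no harm rate and plans no test on harms, so there is no figure to reproduce. The check sets the texts side by side and adds simple arithmetic on exposure and coverage.

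**1. Entry rule.** The sheet is framed around equipment use, the instruction around harms believed to come from the intervention, and the required detail around the activity concerned. All three presuppose that the intervention is present.

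**2. Waiting time.** Before a centre starts there is no intervention, so no event can meet the rule. The expected number of qualifying entries is zero whatever the true injury rate, and a zero there says nothing about background.

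**3. How much waiting time is affected.** The protocol's own statements differ, so a range is needed.
- Assumption A: two centres at each of five start times, the first at month 0, which fits the statement under Data collection timepoints that sites 1 and 6 have no control period. Waiting time = 2 × (0 + 3 + 6 + 9 + 12) = 60 site-months.
- Assumption B: all 10 centres wait 3 to 12 months, as the Control/comparator group paragraph says. The outer bounds are 10 × 3 = 30 and 10 × 12 = 120 site-months.
- The two statements do not fit together. Starts from month 3 to month 12 in three-month steps give (12 − 3)/3 + 1 = 4 start times, whereas Randomisation has five.

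Under either assumption the log gives no background count.

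**4. What the other routes cover.**
- *Questionnaires (Table 2, Data collection timepoints, Statistical analysis).* Roland-Morris back-pain disability and WEMWBS wellbeing need no attribution. They are collected when the control period closes and three and six months after the intervention finishes. Continuous secondary outcomes are modelled with an indicator for whether the intervention is in place. For back pain and wellbeing, then, a comparison between conditions exists. Its limits are that only opt-in staff contribute, sites 1 and 6 have no control measurement and sites 5 and 10 no post-intervention measurement, and neither scale records an acute injury. Centres have more than 100 employees and the target is 27 per centre per collection, so at target fewer than 27/100 = 27% of a centre's staff are covered at any one collection, while all staff may use the activities.
- *Focus groups (Qualitative study, Data collection).* One per intervention site, about 60 people in all, drawn from those who took part in both activities and research. Against more than 10 × 100 = 1,000 employees that is under 60/1,000 = 6%. Staff at centres still waiting are not asked.
- *Sick leave (Table 2)* appears only among measures that may be used for productivity.

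**5. What is left.** Acute injuries, across all staff with access to the activities, are covered only by the sheet, apart from what focus groups happen to bring up. They have no waiting-period counterpart.

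**The case against.** The strongest reply is that the section describes, accurately, a log of suspected intervention harms in a low-risk behavioural feasibility study. No comparison of harm rates is planned, no progression criterion concerns harm, the analyses are declared exploratory, and the protocol wants to keep cost and burden down. That stands, and it limits the weight of the point: nothing is contradicted in the harms text itself, and this is an improvement to the form.

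The reply does not remove the defect. The sheet is already given to each centre and collated from all of them, so the waiting-period collection can return nothing by its own wording.

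A reader might infer more than the documents support:
- *That harms which staff do not recognise are lost to the trial.* They are absent from the log. Back pain and wellbeing are measured without attribution in both conditions, and focus groups may bring out others.
- *That the staff recording harms are untrained, or that theirs is the final causality judgement.* The protocol says neither. It says that they will be made aware of the sheet.
- *That the background statement "One in four members of contact centre staff regularly experience musculoskeletal problems" can be multiplied up to a number of missed harms.* It is a prevalence. It shows that ordinary complaints are common, and gives no rate of missed or misattributed events.
- *That the number of control measurement occasions sizes the problem.* The sheet is a running log, so its unit is site-time.

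**Conclusion.** The point holds in a limited form, as a cheap improvement. The sheet makes staff attribution the condition for entry, so waiting periods give no qualifying entries and injuries that staff do not attribute are not captured on the log. The affected waiting time is 60 site-months if two centres start at each of 0, 3, 6, 9 and 12 months, with outer bounds of 30 to 120 if all 10 centres wait 3 to 12 months. How many injuries that represents cannot be said, because the protocol gives no rate. The gap is confined mainly to acute injuries, since back pain and wellbeing have their own comparison among opt-in participants. In a trial of 10 centres any comparison of injury counts would be descriptive.

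**What to change.** Reword the sheet so that every injury occurring at work is recorded, whatever its believed cause, in all 10 centres from set-up and through the waiting periods, with date, time and activity. The activity field should accept ordinary work as an answer. The study team then assigns relatedness at the existing three-monthly collation. Report the counts descriptively for waiting and post-start site-time, both for all injuries and for those judged related.

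Leave back pain to Roland-Morris, compared between control and post-intervention periods. Logging every new or worse musculoskeletal complaint would be a much larger task: it would gather general health complaints from more than 1,000 staff, many of whom have not joined the evaluation, in a workforce where such complaints are common.

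The cost is a revised form, more entries (most of them unrelated) and some added review at each collation.

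Separately, reconcile Data collection timepoints, Control/comparator group and Randomisation on whether sites 1 and 6 have a waiting period and on how five start times fit the stated range. Waiting site-time cannot be fixed in advance until they agree.

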### Statistical analysis

The statistician will be blind to the allocation of the contact centres. The analysis and presentation of results will adhere to CONSORT guidance [73], and a statistical analysis plan. The analyses will be exploratory to investigate if it’s feasible to fit such a model in a future trial. We will not interpret the results as confirmatory and it is not the primary analysis of the trial.

Sedentary time in the workplace and all continuous secondary outcomes will be analysed using linear mixed effects regression analysis; including site and participant as random effects; and adjusting for calendar time since start of study, season (spring, summer, autumn, winter), and an indicator variable for whether the intervention has been implemented or not as fixed effects. Using observed data from all participants, 95% CI of the intervention effect sizes will provide a guide to indicate the likely effect sizes that we will observe in a future study. Sensitivity analyses will be incorporated to explore the effects of missing data and staff turnover to aid the design of a definitive trial. The assumptions underlying the sample size calculation performed by a similar study [49] will be tested and compared to the estimates we calculate using real data from the feasibility trial (e.g. standard deviation, within-site correlation, intra-cluster correlation coefficient) to inform the power calculation for a future trial. The heterogeneity of quantitative outcomes across sites (e.g. estimated via intra-cluster correlation coefficients) and variability in intervention delivery and processes across sites is of particular interest. Information gathered from this feasibility study will help determine the feasibility of conducting a future multi-site study with a larger number of contact centres.

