# Study Aims and Research Questions

## Study Aims:

*Aim 1:* To test the acceptability and feasibility of implementing the Stand Up for Health intervention in contact centres

*Aim 2:* To assess the feasibility of using a cluster randomised controlled trial study design

*Aim 3:*To scope the feasibility of a future health economic evaluation of Stand Up for Health

*Aim 4:* Consider previous aims under the context of covid-19

### Research questions for Aim 1

1. What is the acceptability, feasibility, and utilisation of the various components of the intervention in a range of contact centres?
2. Does the programme theory and process of implementing the intervention work as intended?
3. Does the programme theory/intervention need adapting and in what ways?
4. Are there differences in delivery of the intervention, between different contact centres? If so what are the reasons for these?

### Research questions for Aim 2

1. Is the study design (cluster RCT) feasible for a confirmatory trial of an intervention to reduce sedentary behaviour in staff working in contact centres?
2. How many clusters and participants per cluster are required for a confirmatory trial?
3. What is the recruitment rate of participants in each cluster and how many are lost of follow-up (e.g. due to staff turnover)?
4. Are the range of study procedures (e.g. recruitment strategies and outcome measurement tools) feasible for a future confirmatory trial?
5. Are there differences in aspects of study procedures (e.g. uptake) between different contact centres? If so what are the reasons for these?
6. What are the preliminary estimates of the variability of primary (reduction of sedentary

behaviour in the workplace) and secondary outcomes within and between contact centres?

### Research questions for Aim 3

Is it feasible to provide estimates of the cost-efficiency of Stand Up for Health from a) an NHS and personal social services (PSS) perspective and b) and employers perspective.

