## Progression criteria

We will proceed to a future larger study if all of the following are satisfied:

1. 95% confidence intervals for the primary outcome includes a clinically relevant reduction in sedentary time of 45 minutes per day or greater in favour of the intervention. This would reflect substantial progression towards accumulating recommended quantity of 2h/day standing/light activity during working hours [54] for employees in predominantly desk-based occupations.
2. Intervention successfully delivered in at least five of the sites within the study period, if at least one person in each site was able to use/experience at least one activity.
3. At least 10% of employees at a site were able to use/experience at least one of the intervention activities in the sites at which the intervention was successfully delivered.
4. Out of all the participants using/experiencing at least one of the intervention activities, primary and secondary outcome data was collected in at least 75% of participants overall.
5. Contamination between sites is low or else it is envisaged that contamination can be addressed in the study design of a future study.
6. It is envisaged that any practical difficulties in delivering the intervention across multiple sites or in measuring effectiveness can be overcome when conducting a future large-scale study.

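### The named mixed model has no site-by-period random effect, so its 95% CI is too narrow if centre effects shift between assessments, and within- and between-period ICCs cannot be separated

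*Protocol*

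**What the plan says.** The protocol's Statistical analysis section names the model: the primary outcome and the continuous secondary ones "will be analysed using linear mixed effects regression analysis; including site and participant as random effects". Its fixed part is described as "adjusting for calendar time since start of study, season (spring, summer, autumn, winter), and an indicator variable for whether the intervention has been implemented". No site-by-period effect or decaying within-site correlation is mentioned, and no interval method or degrees of freedom are given.

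The same section says that the "95% CI of the intervention effect sizes will provide a guide to indicate the likely effect sizes" to be expected in a future study. It commits to estimating several quantities ("e.g. standard deviation, within-site correlation, intra-cluster correlation coefficient) to inform the power calculation for a future trial"). It also limits the status of the model: "We will not interpret the results as confirmatory and it is not the primary analysis of the trial".

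Two other sections depend on the output. The research questions for Aim 2 ask "How many clusters and participants per cluster are required for a confirmatory trial". Progression criteria, item 1, requires that the "95% confidence intervals for the primary outcome includes a clinically relevant reduction in sedentary time of 45 minutes per day or greater", and all six criteria must be satisfied.

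**The concern.** A single constant site effect treats two employees of one centre as equally alike whether they are measured in the same week or many months apart. Under Data collection timepoints and Duration of the intervention, a centre with all three assessments is measured over about nine months: at the end of control, then 3 and 6 months after an intervention of about three months.

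The protocol itself makes centre-specific change over that span plausible. Design and methods anticipates structural, location or organisational change in a single centre. Retention puts annual staff turnover at around 24%. The intervention section says the theories of action are particular to each centre. Calendar time and season can remove only shifts that all centres share.

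Centre-specific variation between assessments is part of the noise against which the intervention contrast is judged, because exposure switches for a whole site at once. If that variation exists and the model has no term for it, the standard error is too small. At stake are the CI used for criterion 1, the CI offered as a guide to future effects, and the correlation inputs for a later trial.

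**Working it through.** **1. The plan's own figures.** 160/6 = 26.67, rounded up to 27 per centre per data collection period; 27 × 10 = 270. The divisor 6 can be reproduced. With five start times three months apart, two sites each, control data at period s and post-intervention data at s+2 and s+3, periods 3, 4 and 5 each have two control sites alongside post-intervention sites: 3 × 2 = 6. With no control data at sites 1 and 6 and no post-intervention data at sites 5 and 10, there are 24 observed site-periods, 8 control and 16 post-intervention. The 160 per arm cannot be checked, because SD, power and ICC are not given. Without a design effect, SD = 45 × √(160/2)/(z₀.₉₇₅ + z_power), which is 144 min at 80% power or 124 min at 90%.

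**2. Assumptions not in the protocol.** Within-period ICC 0.02, 0.05, 0.10; CAC 1.0, 0.8, 0.5; 60% of within-site variance lies between participants; the same 27 people at every assessment of a site; no attrition; no true effect.

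**3. Mechanism.** With total variance 1, site-by-period variance = ICC × (1 − CAC), and residual variance = (1 − ICC) × 0.4. For comparisons within a site over time, the named model counts only residual/27 per assessment, so its SE is roughly √[(residual/27)/(residual/27 + site-by-period)] of the true one.
- ICC 0.05, CAC 0.8: residual/27 = 0.38/27 = 0.0141; site-by-period = 0.010; √(0.0141/0.0241) = 0.76.
- ICC 0.10, CAC 0.8: 0.36/27 = 0.0133; site-by-period = 0.020; √(0.0133/0.0333) = 0.63.

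**4. Simulation.** Restricted maximum likelihood fits to the 24 site-periods with linear calendar time, season and intervention as fixed effects; 500 to 600 runs per row. The Monte Carlo standard error is about 1 point at 94% coverage (√(0.94 × 0.06/600)) and 2 points at 71% (√(0.71 × 0.29/500)). Coverage of the nominal 95% CI, in per cent:

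| ICC | CAC | Model SE / true SE, named model | Named model, ±1.96 SE | Named model, t(8) | With term, ±1.96 SE | With term, t(8) |
|---|---|---|---|---|---|---|
| 0.02 | 1.0 | 0.98 | 93.8 | 97.0 | 94.2 | 96.8 |
| 0.02 | 0.8 | 0.92 | 91.3 | 96.7 | 92.8 | 97.8 |
| 0.02 | 0.5 | 0.80 | 88.5 | 94.0 | 92.7 | 96.7 |
| 0.05 | 1.0 | 0.96 | 93.2 | 95.8 | 93.5 | 96.3 |
| 0.05 | 0.8 | 0.78 | 86.5 | 93.2 | 91.0 | 95.8 |
| 0.05 | 0.5 | 0.67 | 80.2 | 88.2 | 91.8 | 94.2 |
| 0.10 | 1.0 | 0.93 | 91.8 | 96.2 | 92.0 | 96.0 |
| 0.10 | 0.8 | 0.68 | 81.0 | 86.6 | 89.8 | 93.8 |
| 0.10 | 0.5 | 0.52 | 71.0 | 77.6 | 91.4 | 94.4 |

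At CAC 1 the extra term raises coverage by at most 0.4 points; the small shortfall there comes from using a normal quantile with ten sites.

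**5. Effect on criterion 1.** The CI reaches 45 min when estimate + 1.96 × SE ≥ 45. A separate simulation at an assumed SD of 100 min, ICC 0.10 and CAC 0.8 gave a mean model SE of 13.8 min against a true 20.0 min (ratio 0.69).
- Model SE: 45 − 1.96 × 13.8 = 18.0 min needed.
- True SE: 45 − 1.96 × 20.0 = 5.8 min needed.

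Estimates between about 6 and 18 min would therefore fail only because the interval is too narrow. The matching row of the table, at SD 100, has SEs of 12.2 and 18.1 min and a window of about 9.5 to 21 min. The window moves with the assumed SD.

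**6. Correlations.** The named model still returns an ICC close to the truth (means 0.018–0.021, 0.041–0.049 and 0.084–0.093 for true 0.02, 0.05 and 0.10), but it fixes CAC at 1. With the term added, the CAC estimate at true CAC 0.5 has interquartile range 0.00–0.81, 0.03–0.73 and 0.18–0.69 for the three ICCs.

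**The case against.** The strongest reply is that the problem is conditional, and the protocol gives no CAC, ICC or SD. A reader might infer that the CI is too narrow whatever happens. The documents do not support that: at CAC 1 the omission is nearly harmless, and at ICC 0.02 with CAC 0.8 it costs about 1.5 points of coverage. Shifts shared by all centres, such as much of any covid-19 effect, are at least partly absorbed by calendar time and season. This stands, and the point is therefore put conditionally.

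A reader might also infer that normal-based limits are planned. The protocol does not say so. The interval method may be in a statistical analysis plan that is not shown, and its absence here is no finding. With t(8) limits the named model would do acceptably in the milder settings, but coverage would still be 77.6 to 88.2% at ICC 0.10 with CAC 0.8 or 0.5 and at ICC 0.05 with CAC 0.5.

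It would be too strong to say that the correlation needed for the next trial is not estimated. The protocol commits to an ICC and a within-site correlation. Only the split into within-period and between-period ICC is missing, and that split matters only if the next trial is multi-period, which the protocol leaves open. With ten sites the split will be imprecise in any case.

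Finally, the analysis is declared exploratory. That lowers the weight of the point but does not remove it, because a progression criterion rests on the CI. Nor does a narrow interval make progression too easy: at a given estimate below 45 min it can only make criterion 1 harder to meet, and at 45 min or above the criterion is met at any width.

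**Conclusion.** The point holds in conditional form, as a cheap improvement. The protocol itself states a random-effects structure without a site-by-period term, in a design where exposure switches by site and period and where its own description makes centre-specific drift plausible. If CAC is below 1, the 95% CI is too narrow: coverage is about 81 to 91% at CAC 0.8 and 71 to 89% at CAC 0.5.

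These figures rest on the assumed ICCs, a 60:40 split of within-site variance, a full cohort of 27 per site, normal limits for the named model, and the reading that site and participant effects are constant over time. The consequence for progression further assumes that criterion 1 uses the CI from this model, the only one the protocol describes for the primary outcome. The consequence is one of wrongly stopping. The loss of the within- and between-period split is certain under the named model, but matters only for a multi-period successor.

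**What to change.** In Statistical analysis, add a site-by-period random effect to those for site and participant. State that the CI used for progression criterion 1 comes from that model, with a small-sample correction suited to ten sites (for example Kenward-Roger, or t limits on about 8 df), and keep the correction if the site-by-period variance is estimated at zero. Report within-period and between-period ICCs with their uncertainty, alongside the SD and ICC already promised.

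This needs one more variance term, and no new data or design change. The costs are wider intervals, which make an already permissive criterion easier to meet; a site-by-period variance that may be estimated at zero for some outcomes; and a CAC estimate so imprecise that it should enter future sample-size planning as a range, not a single value.
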